### Analysis of efficacy parameters

Merely the criteria of the primary objective will be evaluated inductively. All secondary outcome variables will be analyzed descriptively throughout the distribution across both therapy arms. For criteria that are of side objective, 95% confidence intervals and *p* values will be reported which are based on analogue models like the one for the main objective criterion. Those have a self-explanatory character and do not distinguish between the efficacies of the examined therapies.

### Analysis of main objective criterion

A univariate analysis of covariance (ANCOVA) will be used to generate results for the criterion of the main objective, which was to test whether there would be changes in pain intensity comparing to the beginning of the study to the fifth post-operative day on a 100-mm VAS. For this analysis the main parameter will be measured as a function of group affiliation (graded as a fixed factor on two levels), the baseline measure (linear, fixed covariate), patient expectation (ordinal, fixed factor on five levels), time and duration of surgery (as measured in hours) as well as pain intensity on the day before surgery will be modelled. Within this ANCOVA a *t* test, with a two-sided level of significance of α = 5%, will test whether both intervention groups differ from one another.

Additionally, the progress of VAS changes will be modelled with the help of a mixed linear model. For this model aside from group membership (binary), the VAS score at baseline (linear), time of surgery and patient expectation will be entered as fixed factors and the patient code (graded) will be entered as a random factor. The intra-individual correlation will be assumed to be exponentially decreasing with time. The estimated therapy effect, *p* values and confidence intervals will be based on the relevant *t* test.

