**Methods/design:**

This is a monocentric, double-blind, randomised placebo-controlled trial conducted at the Department of Neurosurgery at the Community Hospital Herdecke, Germany. One hundred study participants are being recruited from inpatients undergoing elective, monosegmental, lumbar microdiscectomy surgery. Patients are randomly allocated to receive homeopathic treatment or placebo in addition to usual pain management after surgery. The primary clinical outcome is pain reduction after 3 days of inpatient care as measured by pain reduction of subjective pain on a 100-mm Visual Analogue Scale (VAS) at the third post-operative day. Statistical analysis will be carried out by means of a covariance model with adjustment for baseline values and patient expectation for all randomised patients.

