## Background

Disc herniation is one of the most common degenerative diseases of the lumbar spine. The incidence for lumbar disc herniation in Germany is 150/100,000 people per year. Sixty out of those 100,000 patients undergo intervertebral disc surgery, resulting in 50,000 operations a year [1]. The prevalence of a herniated disc is estimated to be 20–30% for the age group between 35 and 64 years. In a review of the prevalence of degenerative lumbar disc lesions, Battié et al. reported frequencies for a reduced disc height of 3–56% and for lumbar herniation of 3–63% depending on the design of the study [2]. Moreover, it was noted that only very few studies investigated the frequency of disc herniation with segment-related radiculopathy at all. The results show that the frequency for this incident is in the low single-digit range [3].

Treatment options for a lumbar disc herniation are determined by the duration and presence of the symptoms and the severity of the resulting pain. Besides, the nature of the symptoms (such as weakness or numbness), the patient’s age and further progression of pain relief are important decision-making parameters for conservative therapy or surgery [4]. If medication, physical therapy, and/or other non-surgical treatments have not led to a significant symptom improvement over 6 weeks, a relative indication for surgery is given [4]. Patients who undergo lumbar surgery as well as patients who are not operated on both improve within 2 years. However, there is a trend with regard to pain reduction in favour of patients who undergo lumbar disc herniation surgery [5]. This is underpinned by the 4-year results of the Spine Patient Outcomes Research Trial (SPORT) which showed significantly better results in the pain scores in surgical patients compared to the conservatively treated group [6].

Depending on the main diagnosis, in 2010, patients with lower back problems were subjected to back surgery in 38% of the cases [7]. Since the introduction of the Diagnosis Related Groups (DRG), the length of stay in Germany after minimal invasive surgery is about 3–4 days if no adverse events (AEs) occur, which is comparable with international data [8].

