### Aims

The aim of the study is to investigate the effect of *Hypericum* C200 in post-operative pain management. The primary aim of the study is to assess the reduction of subjective pain on the 100-mm VAS at the third post-operative day. In consideration of the side effects of conventional pain medication and the potential benefit of *Hypericum* in wound healing and neural pain reduction, it is reasonable also to investigate the dosage of conventional analgesic intake between the groups as a secondary outcome measure.

Finally, the reduction of subjective pain on the VAS at the fifth post-operative day and the development of sensory and affective pain perception (as assessed using the Pain Experience Scale ‘Schmerzempfindungsskala’ (SES)) between the groups, as well as the amount of post-surgical intake of analgesic/anti-inflammatory agents, are also secondary outcomes.

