## Methods/design

### Study design

The study will be a randomised, placebo-controlled, double-blind trial with a 3–5-day duration.

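### The one confirmatory test is set at post-operative day 5, but the abstract and aims make day 3 the primary time point and call day 5 secondary

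*Protocol article*

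**What the plan says.** The abstract sets the primary time point at day 3: "The primary clinical outcome is pain reduction after 3 days of inpatient care", measured by "pain reduction of subjective pain on a 100-mm Visual Analogue Scale (VAS) at the third post-operative day". The Aims section agrees: "The primary aim of the study is to assess the reduction of subjective pain on the 100-mm VAS at the third post-operative day". It then names "the reduction of subjective pain on the VAS at the fifth post-operative day" in a list that closes with the words "are also secondary outcomes".

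The section on analysis of the main objective criterion specifies the ANCOVA in full. There the criterion is "changes in pain intensity comparing to the beginning of the study to the fifth post-operative day on a 100-mm VAS", and the group comparison is a two-sided t test at 5%. The section on efficacy parameters limits inferential testing to the primary objective and makes every secondary variable descriptive. Confidence intervals and p values for secondary variables carry no claim of efficacy.

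The Outcomes section defines a daily mean of four VAS readings but names no day for the primary endpoint. The sample size section names no day either.

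**The concern.** The primary time point decides which comparison carries the trial's 5% claim. Under the abstract and aims that is day 3, and a day-5 result is descriptive. Under the analysis section it is day 5, and the day-3 result, which the article calls primary, has no specified confirmatory test. The two days can give different answers. A reader of the final report could not tell from this document which one had been prespecified. Whoever finalises the analysis would also have textual support for either choice.

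**Working it through.** **1. The statements side by side**

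- Abstract, Methods/design: primary outcome, day 3.
- Aims: primary aim, day 3; VAS at day 5 secondary.
- Outcomes: primary endpoint is VAS pain reduction, no day given. Averaging four readings within a day does not select a day.
- Sample size calculation: no day given.
- Analysis of efficacy parameters: only the primary criterion is tested inferentially.
- Analysis of main objective criterion: change to day 5, two-sided 5% test.

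Day-5 VAS cannot be both a descriptive secondary outcome and the one criterion tested confirmatorily.

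**2. Does the sample size settle the day?**

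Inputs from the sample size section: difference 15 mm, SD 20 mm, two-sided α = 0.05, power 0.90.

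- Normal approximation: n per group = 2 × (1.960 + 1.282)² × 20² / 15² ≈ 37.4, rounded up to 38.
- Exact t test: 38.35, rounded up to 39.
- Stated: 40 per group, where power is 0.918 (normal) or 0.912 (t). The plan's figure is reproduced to within two patients.
- With 20% non-compliance: 40 / 0.80 = 50 per group, as stated.

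None of these inputs is tied to a day. The calculation is the same for day 3 and day 5, so it cannot show which was meant, and correcting the day does not alter it.

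**3. Error rate if the day were chosen after the data are seen**

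Let Z3 and Z5 be the day-3 and day-5 test statistics, standard normal under the null with correlation ρ. The chance that at least one is significant is

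1 − P(|Z3| ≤ 1.96 and |Z5| ≤ 1.96).

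The documents do not give ρ, so it is an assumption shown over a range:

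- ρ = 0: 0.0975
- ρ = 0.5: 0.0907
- ρ = 0.7: 0.0835
- ρ = 0.8: 0.0781
- ρ = 0.9: 0.0704
- ρ = 0.95: 0.0646

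Over ρ = 0.5 to 0.9 this is 9.1% down to 7.0%. If one day is fixed beforehand, whichever it is, the level is 5%.

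**The case against.** **The day-5 wording may describe the observation window.** On this reading the phrase gives the span of follow-up and not the tested time point. The reading is weak. The ANCOVA is described as univariate, and the course over time has its own mixed linear model, introduced as an addition.

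**The ANCOVA may belong to day 3, with a slip in the analysis section.** The abstract follows the day-3 outcome directly with a covariance model adjusted for baseline and expectation. This stands. It makes a drafting error likely and supports calling the endpoint inconsistent. A reader might go further and infer that the trial is set to test the wrong endpoint. The documents do not show that, because they do not say which statement governs.

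**The statistical analysis plan may resolve it.** The article defers patient evolution, non-compliant cases and missing values to that plan, but not the choice of primary time point. The conflict lies between statements made in this document, so it is not an omission.

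**The 5% level is not already broken.** This is right. The inflated figures need an analyst who looks at both days and then picks one. A day-5 test run exactly as written would keep 5%.

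**Loss at day 5 is not shown.** A reader might infer that many patients will have gone home by day 5, so that a day-5 primary analysis would rest heavily on imputation with missingness driven by recovery. The support offered is that "the length of stay in Germany after minimal invasive surgery is about 3–4 days", together with "placebo-controlled, double-blind trial with a 3–5-day duration". The first is a general background figure for Germany, not for this hospital or trial. Study medication, the pain experience scale and data collection are all planned through day 5. The article gives neither discharge criteria nor any statement that discharged patients stop completing the VAS, which they fill in unaided. More frequent missing values at day 5 than at day 3 are possible, and the article gives no share.

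**Conclusion.** The contradiction is real and must be resolved before unblinding. Two statements make day 3 primary, one of which also makes day 5 secondary, while the full specification of the confirmatory test uses day 5. No other section decides between them.

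The certain consequence is that the prespecified primary comparison cannot be identified from the document. The error-rate consequence is conditional: about 7.0% to 9.1% in place of 5%, only if the day is chosen after the data are seen, and only under the assumed correlation of 0.9 to 0.5. More missing data at day 5 is a possibility and not a finding, and the conclusion does not rest on it. Day 3 is the better supported reading, but the intention is for the sponsor to confirm.

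**What to change.** The sponsor confirms in writing, before unblinding, that day 3 is the intended primary time point. Then:

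1. In the section on analysis of the main objective criterion, change the end of the comparison from the fifth to the third post-operative day, in line with the abstract and aims.
2. Keep the other model terms listed there: baseline value, expectation, the surgery timing and duration terms, and pain the day before the operation.
3. State that the day-5 ANCOVA is secondary and descriptive.
4. Name the same day in the Outcomes section and in the statistical analysis plan.

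The cost is a few words in the protocol and the analysis plan, submitted as an amendment by the route the article already describes. No new data are needed and the sample size does not change. The statistician is to stay blinded until the end of the study, so the correction can be made without knowledge of the results by group.

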### Outcomes

The primary endpoint of this study is pain reduction as measured by the subjective pain sensation on a straightforward 100-mm Visual Analogue Scale (VAS). The VAS will be handed out to patients for their individual evaluation of their subjective pain perception. For each entry, a VAS scale is designated on a separate sheet, so patients will be able to fill in the scale independently. The pages will then be collected as source data and kept in each patient file. Measurement of pain will occur four times a day and the average will be determined for each day.

The secondary endpoint is the amount of post-surgical intake of analgesic / anti-inflammatory agents. The number and dosages (in milligrammes) of the medical application will be collected for standard as well as the individually requested medicine. All occurring AEs will be descriptively recorded in the Case Report Form (CRF). Data regarding medication requested and taken by the patient will be extracted from the medical record folder.

In order to be able to describe the post-operative pain more precisely the standardised ‘Pain Experience Scale’ (German: Schmerzempfindungsskala (SES)) will be applied during study visits T− 1, T1, T3 and T5 once a day (see also Fig. 2 and Additional file 1: Standard Protocol Items: Recommendations for Interventional Trials (SPIRIT) Checklist). Due to their self-explanatory character, supervision in completing the VAS and SES will not be necessary.

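### The additional mixed model for the course of VAS lists no post-operative day and no group-by-day term, so it yields one day-averaged group difference, which can differ from the day-3 effect

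*Protocol article*

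**What the plan says.** The section on the analysis of the main objective criterion first sets out the primary ANCOVA and then a second model: "Additionally, the progress of VAS changes will be modelled with the help of a mixed linear model". Its specification is explicit:

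- Fixed part: "aside from group membership (binary), the VAS score at baseline (linear), time of surgery and patient expectation will be entered as fixed factors".
- Random part: "the patient code (graded) will be entered as a random factor".
- Residual structure: "The intra-individual correlation will be assumed to be exponentially decreasing with time".
- Reported result: "The estimated therapy effect, *p* values and confidence intervals will be based on the relevant *t* test". A single therapy effect is meant.

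The data for this model come from the Outcomes section: "Measurement of pain will occur four times a day and the average will be determined for each day". Each patient thus contributes one VAS value per day. The Study design section gives a duration of three to five days. The Aims name the time point of main interest: "The primary aim of the study is to assess the reduction of subjective pain on the 100-mm VAS at the third post-operative day".

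**The concern.** The stated purpose and the listed terms do not fit together. Group, baseline VAS, time of surgery and expectation each take one value per patient. Time of surgery is not a substitute for study day: the ANCOVA in the same section pairs it with duration of surgery, so it is a feature of the operation. Study time appears only in the correlation, which affects weights and standard errors but not the fitted mean. The model thus assumes that mean pain does not change over the post-operative days and that the group difference is the same on each of them.

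At stake is the reading of a supportive result. The trial's rationale is a radicular pain that sets in from the third post-operative day, so an effect that varies by day is plausible. A single averaged coefficient, reported with a p value and confidence interval as the result of a model for progress, could then appear to disagree with a day-specific analysis only because of how the model was built.

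**Working it through.** **Inputs from the protocol article.** Smallest relevant difference 15 mm, SD 20 mm (the wording is garbled; read as an SD of 20 mm), power 0.90, two-sided alpha 0.05, 40 per group before and 50 per group after allowance for non-compliance (Sample size calculation).

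**Assumed inputs.** The article gives no daily effect profile, no daily means and no correlation value. Those used below are assumptions, varied over a range.

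**1. The plan's own figure.** n per group = 2 × (1.960 + 1.282)² × 20² / 15² = 37.4, rounded up to 38. The exact noncentral t calculation gives 39 (power 0.905), and 0.912 at n = 40. The stated 40 is reproduced within two patients, and 40 / 0.80 = 50. This concerns the primary test and does not depend on the mixed model.

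**2. What the listed model estimates.** With only patient-constant fixed effects and a common visit schedule, the generalised least squares group coefficient is the sum of w_d × δ_d. Here δ_d is the group difference on day d and w = V⁻¹1 / (1′V⁻¹1). For a correlation ρ^|i−j| over days 1–5, the weights are proportional to (1, 1−ρ, 1−ρ, 1−ρ, 1), with sum 5 − 3ρ. The random patient factor does not change them. If V = τJ + (1−τ)R and x = R⁻¹1, then Vx is a multiple of 1, so V⁻¹1 is proportional to x.

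**3. Results for a true day-3 effect of 15 mm, complete days 1–5.**

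| Assumed effect, days 1–5 (mm) | Formula | ρ = 0 | 0.2 | 0.5 | 0.8 |
|---|---|---|---|---|---|
| 15-15-15-15-15 (constant) | 15 | 15.0 | 15.0 | 15.0 | 15.0 |
| 5-10-15-20-25 (linear) | (75 − 45ρ)/(5 − 3ρ) | 15.0 | 15.0 | 15.0 | 15.0 |
| 0-0-15-15-15 (onset on day 3) | (45 − 30ρ)/(5 − 3ρ) | 9.0 | 8.9 | 8.6 | 8.1 |
| 5-10-15-15-15 (plateau) | (60 − 40ρ)/(5 − 3ρ) | 12.0 | 11.8 | 11.4 | 10.8 |
| 0-7.5-15-7.5-0 (peak on day 3) | 30(1 − ρ)/(5 − 3ρ) | 6.0 | 5.5 | 4.3 | 2.3 |

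**4. Shorter follow-up.** For the linear profile, if all patients have only days 1–3, the coefficient is (5 + 10(1−ρ) + 15)/(3 − ρ) = 10 mm. With days 1–4 it is (5 + 25(1−ρ) + 20)/(4 − 2ρ) = 12.5 mm. The agreement with day 3 in the linear case therefore requires all five days.

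**5. With day and group-by-day added.** In simulated complete data (80 patients, 150 replicates, random intercept plus autoregressive errors, falling daily means), the day-3 contrast averaged 14.3 to 15.6 mm across four profiles, against a true 15 mm. The listed model gave 14.6 (constant), 15.5 (linear), 7.6 (onset on day 3) and 3.1 mm (peak on day 3), in line with the formulas up to simulation error.

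**6. Early discharge, constant effect of 15 mm.** Simulation with 400 per arm and 40 replicates under three correlation structures, analysing observed days only, gave for the listed model:

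- Daily means 50, 42, 35, 30, 27 and discharge of patients with low day-3 pain: 13.1–14.1 mm.
- The same means, with 40% discharged at random: 14.8–15.1 mm.
- Flat means, low-pain discharge: 14.8–15.2 mm.
- Means 40, 38, 42, 42, 40, low-pain discharge: 14.8–15.3 mm.

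Of these scenarios, only the one that combines a falling mean with pain-dependent discharge shows a bias: 15 − 14.1 = 0.9 to 15 − 13.1 = 1.9 mm.

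**The case against.** A reader might infer that this model misstates the day-3 effect as such. The documents do not support that. The mixed model is introduced as an addition to the ANCOVA and is nowhere presented as the day-3 estimator. A day-averaged difference is a legitimate quantity, and it equals the day-3 effect when the effect is constant, or linear with all five days observed. A reader might also infer that early discharge will bias the result. That needs a declining mean and discharge that depends on pain, and the article gives neither a daily course nor a discharge rule. The plan also multiply imputes missing total scores, which the discharge simulation leaves out, although whether imputation covers each day of this model is unclear. All of this stands and limits the claim.

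It can also be said that the article is a condensed text which leaves the description of how patients develop within each group to a later SAP. This carries less weight. The article does not stay silent on the model: it lists the fixed terms, the random factor, the correlation and the reported quantities. A later SAP can correct the list, but the list as printed does not serve its purpose.

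Lastly, only the primary criterion is tested inferentially, so no decision of the trial rests on this model. That is correct and sets the weight of the point.

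**Conclusion.** The point holds in a limited form. As specified, the additional model cannot describe the progress of VAS or a day-specific group difference. This follows from the listed terms alone and needs no simulation. Whether the single coefficient departs from the day-3 effect depends on the effect profile and on length of follow-up. With a true 15 mm at day 3, it ranges from no departure (constant effect) through 10.8–12.0 mm (plateau) to 8.1–9.0 mm (onset on day 3) and 2.3–6.0 mm (peak on day 3). The possible discharge bias of about 1–2 mm rests on two further assumptions. The defect lies in a supportive analysis; the primary ANCOVA and the sample size stand as they are. That the ANCOVA text names day 5 while the Aims name day 3 is a separate contradiction and is not part of this point.

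**What to change.** In the SAP, add post-operative day (categorical, days 1–5) and the group-by-day interaction to the fixed effects of the mixed model. Name the day-3 contrast, with its confidence interval, as the supportive estimate, and report the other days descriptively. If the single coefficient is kept as well, label it as a group difference averaged over days.

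The cost is a change of wording and 4 + 4 = 8 further fixed-effect parameters, against up to 100 × 5 = 500 patient-days. No new data or patients are needed, and the primary analysis does not change.

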### Auditing

The Center for Clinical Studies at Witten/Herdecke University (ZKS UW/H) will monitor and examine abidance with the study protocol.

### Confidentiality

The relevant regulations of the data protection legislation will be entirely fulfilled. All appropriate and necessary precautionary measures will be met in order to perpetuate the confidentiality of medical data and personal information.

### Regulatory and ethical approval

The application has been approved to the competent ethics committee (Witten/Herdecke University) and the Federal Institute for Drugs and Medical Devices (Bundesinstitut für Arzneimittel und Medizinprodukte, BfArM, Bonn, Germany).

This study is in compliance with the Helsinki Declaration and with the International Conference on Harmonisation (ICH) – Good Clinical Practice.

In case of necessary protocol amendments the amendment will be submitted to the ethics committee and competent authority and implementation will be done after approval. Due to the study design (monocentric, investigator-initiated trial) and close contact between study team, sponsor and site, a separate communication plan is not necessary.

